## Abstract

**Background:**

Severe mental disorders, a leading cause of disability has become a major public health problem. In order to promote mental health, a series of programs have been promulgated by the Chinese government. However, economic evaluations of such programs are lacking. The purpose of this study is to develop and validate an economic model to assess the cost and health outcomes of the LEAN (Lay health supporters, E-platform, Award, and iNtegration) program, and to perform an economic evaluation of LEAN versus the nationwide community-based mental health program that provides free antipsychotic medications.

**Methods:**

A cost-effectiveness and cost-utility analysis of the LEAN intervention will be performed. A Markov model will be developed, validated and used to assess and compare the costs and outcomes for the LEAN intervention versus nationwide community-based mental health program. The calculated sample size is 258 participants for the analysis. A societal perspective will be applied with the time horizon of 1-year after the termination of the LEAN program. The cost-utility will be measured primarily using Quality Adjusted Life Years and the cost-effectiveness will be measured using number of relapses and number of re-hospitalizations avoided 6-month after the intervention. Univariate and probabilistic sensitivity analysis will be conducted for the analysis of uncertainty.

**Discussion:**

If proven cost-effective, this study will contribute to the nationwide implementation of the program, not only for schizophrenia but for all kind of severe mental disorders. Markov model developed as part of the study will benefit potential researchers in analyzing cost-effectiveness of other programs. The Chinese context of the study may limit the generalizability of the study results to some extent.

**Trial registration:**

This study was registered in a Chinese Clinical Trial Registry (ChiCTR2000034962) on 25 July 2020.

## Background

With a rapid change in the socio-economic development over the past three decades, the rise in the incidence rates of severe mental disorders has become a major public health problem in China [1]. Severe mental disorders, which include schizophrenia, bipolar disorder and severe depression are complex psychiatric disorders that manifest into disabling conditions of hallucinations, delusions, and disordered thinking and behavior [2]. Due to their disabling effects, it has devastating costs to patient, families, and society. In China, the burden of mental disorders account for 13% of all non-communicable diseases burden and is expected to increase by 10% by the year 2025 [3], warranting an urgent prioritization of programs focused on targeted prevention and effective treatment.

Effective treatment is available for mental disorders, but the shortage of mental health professionals and nonadherence to treatment have led to large treatment gaps in China [4, 5]. A systematic review of the studies that had used the internet- and mobile-based interventions to overcome the barrier in providing mental healthcare showed clinically and cost-effective results [6]; however, no studies included in the review were conducted among the Chinese population. To understand the potential role of mobile intervention to help address the challenge in providing mental healthcare, our study team conducted a randomized controlled trial to leverage the power of family members by using mobile texting to assist in formal patient care in a resource constraint rural area in China. Our approach, called “LEAN” (Lay health supporters, E-platform, Award, and iNtegration of services with the health system), involved the recruitment of lay health supporters aided by text messages for medication reminders, health education, monitoring of early signs of relapses, and facilitating linkage to primary healthcare to the patients with schizophrenia [7, 8]. LEAN intervention adapted the Health Belief Model (HBM) to target individual components of LEAN from the empirical literature on task shifting and mHealth to improve patient adherence to medication [9]. With the increasing prevalence of the severe mental disorder, there is also an increase in the burden experienced by caregivers and health care providers. Nonadherence to antipsychotic medication is one of the major concerns among these patients that increases the risk of relapse and re-hospitalization [10], suggesting a need of the development of strategies that would reduce medication nonadherence [5, 11].

A nationwide mental health program (the 686 program) was launched in China in 2005 [12] with an aim to address the challenges around the lack of integration between hospital and community health care for managing severe mental disorders. The program moved specialty mental health services into community settings providing outreach services into the community. Although the program has been able to improve access to care, it has not been able to reach its ambitious goals due to enormous challenges in the delivery of the program, greater commitment of resources, and limited available services in the community [12, 13]. Potentially, a simple, easy-to-implement and sustainable service model that can be efficient even in the presence of few mental health professionals and small mental health budgets like LEAN intervention can bring significant benefits to China’s vast population of people, not only with schizophrenia but with other kinds of severe mental disorders too. Results of the LEAN intervention showed significant improvement in medication adherence, symptoms and functioning, reduction in the risk of relapses (defined as an overall and marked increase in symptoms assessed by the health professionals through interviewing patients and family members according to the 686 Program protocol) and re-hospitalizations among patients with schizophrenia [7]; however, the study did not collect sufficient cost data and failed to analyze and report the cost-effectiveness and cost-utility of the intervention.

As a decision to adopt a new strategy or service by health policy decision-makers depends on several factors such as the ability and willingness to pay for marginal health benefits, the effectiveness of the service, and the level of need in the community. Hence, there is a need for the development of a model that can be used to estimate the cost-effectiveness and cost-utility of this novel approach that could demonstrate the added value of the program over the existing program. Hence, the objective of this study is: (i) to develop an economic model to assess the cost and health outcomes of LEAN intervention from a societal perspective and validate the model and (ii) to assess the cost-effectiveness and cost-utility of the LEAN intervention versus the 686 Program alone.

## Methods/design

### Study design

This will be a cost-effectiveness analysis (CEA) and cost-utility analysis (CUA) of a randomized controlled trial that will compare people with schizophrenia who received the 686 Program alone (control group) with those who received the LEAN intervention along with the 686 program (intervention group) that delivered mobile phone text messaging (Table 1). CEA, the most commonly employed type of economic analysis [14] will compare the costs of averting the number of relapses and the number of re-hospitalizations in LEAN intervention as compared to the 686 program. The added value of the LEAN intervention over the 686 Program will be captured through the incremental cost-effectiveness ratio (ICER). For CUA, the effects of an intervention will be expressed as a measure of ‘utility’, commonly measured using the quality-adjusted life-year (QALY) [14]. The study will adopt a broad societal perspective on value, specifically to incorporate all health care costs such as direct medical cost of identifying individuals with schizophrenia and their medication adherence, and all health effects such as patient symptoms, functioning, relapses, and re-hospitalizations [15]. The indirect non-medical costs will include production losses related to reduced efficiency at work and absenteeism at work [16].

**Table 1 Tab1:** Types of economic analysis and economic costs of the LEAN intervention

Type of analysis	Cost category	Costs	Outcome (effect)	Results expressed as:
CEA	• Cost of human resources • Cost of intervention • Cost of using medical resources	Monetary units (CNY)	Effect of intervention (number of relapses and re-hospitalizations averted	• Cost per relapse and re-hospitalization averted • ICER
CUA	• Cost of identifying individuals with schizophrenia and their medication adherence • Cost of assessing change in symptoms and functioning	Monetary units (CNY)	Healthy lifetime gained (QALYs)	Cost per QALY gained

*CEA* Cost-effectiveness analysis, *CUA* Cost-utility analysis, *CNY* Chinese yuan, *ICER* Incremental cost-effectiveness ratio, *QALY* Quality-adjusted life-year

The disease progression model as defined by McGorry et al. [17] that states different clinical staging of psychiatric disorders has been used to develop the basic design of the model. The final framework of the Markov model will be decided after the consultation with mental health experts, public health experts, and experts in economic modeling.

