### Study sample

Participants were randomly selected from the community-dwelling villagers having a primary diagnosis of schizophrenia in the parent study and were randomized 1:1 into two groups. Participants were selected if they were community-dwellers, were enrolled in the 686 Program, had a primary diagnosis of schizophrenia, were on oral psychotropic medications, and physically resided in 1 of 9 rural townships of Liuyang municipality. Participants were excluded from the study if they were hospitalized due to schizophrenia at the time of recruitment, had missed the most recent three consecutive past drug refills, or were physically incapable of using voice or text messaging. The primary outcome of LEAN trial was medication adherence assessed by unannounced home-based pill-counts; secondary outcomes included patient-level functioning assessed using 12-item World Health Organization Disability Adjustment Scale 2.0 (WHODAS 2.0) [18, 19], the severity of symptoms assessed by Clinical Global Impression in Schizophrenia (CGI-Sch) [20], relapse, and re-hospitalization. Outcome data were collected at baseline during the recruitment process and at 6 months after the implementation of LEAN. In addition to the outcome data collected as part of the trial, we will do additional fieldwork to collect program cost (i.e., cost data and effectiveness data) of the implemented LEAN intervention. Trained research assistants (RAs) will be responsible for conducting interview using survey questionnaire with the lay-health workers and family members to collect program cost data. RAs will also be responsible for obtaining the signed informed consent form from the participants. On the consent form, participants will be asked if they agree to use of their data and for permission for the research team to share relevant data with people from the university taking part in the research or from regulatory authorities, where relevant.

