Intervention cost	• Cost of training in preparation for LEAN • Cost of identifying individuals with schizophrenia • Cost of assessing medication adherence • Cost of message development and management • Cost of phones • Cost of texting to patients and lay-health supporters	Continuous	Cost estimating tool	Fieldwork to be conducted as part of the study, parent study
Human resource cost	Cost of family members, lay health supporters, and health professionals (village doctors, mental health administrators, and psychiatrists)	Continuous	Cost estimating tool	Fieldwork to be conducted as part of the study
Medication cost	Antipsychotics cost incurred due to increased adherence	Continuous	Cost estimating tool	Fieldwork to be conducted as part of the study
Indirect non-medical costs: • Efficiency at work Absenteeism at work	• Number of days with reduced efficiency due to feeling ill • Number of days absent from work	Continuous	TiC-P	Fieldwork to be conducted as part of the study

Parent study is the LEAN intervention

*interRAI MH* inter Resident Assessment Instrument-Mental Health, *WHODAS* World Health Organization Disability Assessment Schedule, *CGI-Sch* Clinical Global Impression in Schizophrenia, *TiC-P* Trimbos/iMTA questionnaire for Costs associated with Psychiatric Illness

Costs will be estimated using quantities of resource used and prices. The price will be estimated using existing market prices or shadow prices (the estimated price of a good or service for which no market price exists). Costs can be fixed (that cannot be changed) or variable (flexible and changes with productivity level); the sum of both these costs will be considered as the total cost. We will develop a standardized cost collection tool and will validate it before we collect new data. For the interpretation of costs of LEAN intervention, we will estimate the incremental change to total costs.

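### Table 1 gives the cost-utility analysis a narrower cost set than the cost-effectiveness analysis, so cost per QALY as tabulated would leave out LEAN's delivery cost and any savings in care

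*Protocol article*

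**What the plan says.** Table 1 in Study design has one row per analysis. The cost-effectiveness row lists "Cost of human resources • Cost of intervention • Cost of using medical resources". The cost-utility row lists "Cost of identifying individuals with schizophrenia and their medication adherence • Cost of assessing change in symptoms and functioning", and its result is "Cost per QALY gained". The two rows share no cost item.

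The text above the table is broader. The societal perspective is "specifically to incorporate all health care costs such as direct medical cost of identifying individuals with schizophrenia and their medication adherence", and "The indirect non-medical costs will include production losses related to reduced efficiency at work and absenteeism at work".

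The Cost data section plans to collect human-resource, intervention, project-management, medication, outpatient, inpatient and productivity costs, with no split between the two analyses. It says that LEAN will be judged on the change in total cost. Table 2 places "Cost of identifying individuals with schizophrenia • Cost of assessing medication adherence • Cost of message development and management" inside the intervention cost, beside training, phones and texting.

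The ICER section defines the ratio per QALY. Its numerator is the cost of the LEAN programme minus that of the comparator programme.

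**The concern.** Both analyses compare the same two programmes in the same patients. They should differ in the denominator (events averted or QALYs), not in the incremental cost. As tabulated, the numerator for cost per QALY contains neither the cost of running LEAN nor any change in hospital and outpatient care. Those are the main ways in which the programme could cost or save money.

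The items that the row does keep look largely like case-finding and outcome measurement. Cost per QALY is the result most readily compared with other programmes, and the article intends its findings to inform national roll-out. The two analyses could also disagree simply because they were costed differently.

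**Working it through.** The article states no unit cost, incremental cost, QALY difference or ICER, so there is no figure to reproduce. The check applies its own formula, ICER = (CT − CC)/(ET − EC), to the two cost sets.

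**Notation, per patient**
- L: extra cost of delivering LEAN (training, messages, phones, texting, human resources, management).
- X: net change in medication, outpatient, inpatient and productivity costs; negative if LEAN saves.
- I_T and I_C: identification and assessment cost in the LEAN and control arms.
- dQ: QALY gain.

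**Formulas**
- Full cost set: ICER = [L + X + (I_T − I_C)]/dQ.
- Table 1 cost-utility row: ICER = (I_T − I_C)/dQ.

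L and X are absent from the second formula whatever their values. If L + X is positive, the row understates cost per QALY. If savings exceed delivery cost, so that L + X is negative, the row hides that saving.

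**Are I_T and I_C equal?** Two places in the article point in different directions.
- Study sample: participants "were enrolled in the 686 Program, had a primary diagnosis of schizophrenia" and were then randomised 1:1, with outcomes collected at baseline and 6 months and no difference by arm described. This makes equal cost plausible.
- Table 2: identification and adherence assessment are filed under the intervention cost, which suggests a cost of LEAN only.

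Both cases are therefore shown.

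**Illustration.** All values are assumed and none comes from the article: I_T = 50 to 200 CNY, L = 200 to 3,000 CNY, dQ = 0.01 to 0.05, X = 0.

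| Numerator | I_C = I_T | I_C = 0 (LEAN only) |
|---|---|---|
| Table 1 cost-utility row | 0/dQ = 0 | 50/0.05 = 1,000 to 200/0.01 = 20,000 |
| Delivery cost included | 200/0.05 = 4,000 to 3,000/0.01 = 300,000 | (200 + 50)/0.05 = 5,000 to (3,000 + 200)/0.01 = 320,000 |

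Entries are CNY per QALY. In the right-hand column the ratio of the two results is (L + I_T)/I_T, which does not depend on dQ. It runs from (200 + 200)/200 = 2 to (3,000 + 50)/50 = 61.

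**Could the row be additive,** listing extras on top of the cost-effectiveness costs? The table does not say so. Table 2 already counts identification and adherence assessment within the intervention cost, which is an item of the cost-effectiveness row, so adding them again would count them twice. The cost of assessing symptoms and functioning appears neither in Table 2 nor in the Cost data list.

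**The case against.** The strongest reply is that Table 1 is a loosely drafted overview and that the analysis text already has the right numerator. Much of this stands. The ICER section puts LEAN's programme cost into cost per QALY. Cost data speaks of total cost. The Fig. 1 caption and Model development describe one Markov model whose states carry both costs and QALYs. The uncertainty analysis names intervention costs as a key parameter. The table is also not exhaustive, since the cost-effectiveness row names neither medication nor productivity costs. Study design introduces identification and adherence only as an example. So the documents do not show that the narrow numerator will be used, only that the article specifies two different ones. They do not say which governs, and Table 1 attaches the ICER label to the cost-effectiveness row alone, so the formula does not plainly override the cost-utility row.

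Three stronger readings are tempting and should not be adopted.
- A reader might infer that identification and assessment costs are the same in both arms, so that cost per QALY would be near zero whatever LEAN costs. Equality is only an inference from Study sample, and Table 2 cuts against it.
- A reader might infer that Table 2 biases the cost-effectiveness analysis against LEAN by charging it with common costs. That rests on the same unstated premise.
- A reader might conclude that these costs should leave the base case altogether. Study design names identification and adherence as costs of the chosen perspective, and a roll-out may need both.

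**Conclusion.** The point holds as an inconsistency with a real consequence. The Table 1 cost-utility row is narrower than the cost-effectiveness row and contradicts the stated perspective, the total-cost approach and the ICER formula. Followed as written, it makes cost per QALY independent of LEAN's delivery cost and of care avoided; this needs no numerical assumption. A result of about zero needs the further assumption of equal identification and assessment costs between arms, which is plausible but unstated.

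The understatement of 2 to 61 times applies only to the assumed ranges, with those costs charged to LEAN alone and X set to zero. With real savings in care, the error could run the other way. The row should be corrected before analysis, although the rest of the text already points to the full numerator.

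**What to change.** Correct the cost-utility row of Table 1 so that both analyses use the same incremental cost set, already planned under Cost data: intervention, human resources, project management, medication, outpatient and inpatient care, and productivity losses. The ICER section opens by referring to a healthcare-sector perspective, so state that productivity losses enter under the societal perspective. Delivery and medical-care costs belong under either.

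Count identification and adherence-assessment costs once. In Table 2, state which of them are part of delivering LEAN and which are research measurement common to both arms, and say the same for symptom and functioning assessment, so that only costs that differ between arms enter the increment.

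This is an edit to two tables and a sentence of text. The cost categories are already planned for collection, so no new data are needed.

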### Setting and duration

The LEAN trial was implemented in 9 rural townships (total population 356,900) of Liuyang municipality, Hunan Province, in central China. In this parent trial, the intervention group received LEAN intervention along with the 686 Program, while the control group received only the 686 Program that lasted from December 15, 2015 to June 15, 2016 for the duration of 6 months (Fig. 1).

**Fig. 1 Fig1:**
[figure not shown]
Basic design of Markov model illustrating different states of mental health through which an individual with schizophrenia could transition. Each state is associated with the cost and value of quality-adjusted life-year (QALY) gained. All states may also progress to death or disability

### Study sample

Participants were randomly selected from the community-dwelling villagers having a primary diagnosis of schizophrenia in the parent study and were randomized 1:1 into two groups. Participants were selected if they were community-dwellers, were enrolled in the 686 Program, had a primary diagnosis of schizophrenia, were on oral psychotropic medications, and physically resided in 1 of 9 rural townships of Liuyang municipality. Participants were excluded from the study if they were hospitalized due to schizophrenia at the time of recruitment, had missed the most recent three consecutive past drug refills, or were physically incapable of using voice or text messaging. The primary outcome of LEAN trial was medication adherence assessed by unannounced home-based pill-counts; secondary outcomes included patient-level functioning assessed using 12-item World Health Organization Disability Adjustment Scale 2.0 (WHODAS 2.0) [18, 19], the severity of symptoms assessed by Clinical Global Impression in Schizophrenia (CGI-Sch) [20], relapse, and re-hospitalization. Outcome data were collected at baseline during the recruitment process and at 6 months after the implementation of LEAN. In addition to the outcome data collected as part of the trial, we will do additional fieldwork to collect program cost (i.e., cost data and effectiveness data) of the implemented LEAN intervention. Trained research assistants (RAs) will be responsible for conducting interview using survey questionnaire with the lay-health workers and family members to collect program cost data. RAs will also be responsible for obtaining the signed informed consent form from the participants. On the consent form, participants will be asked if they agree to use of their data and for permission for the research team to share relevant data with people from the university taking part in the research or from regulatory authorities, where relevant.

